## Abstract

**Background:**

Preterm infants often experience physiological instability and immature feeding coordination, which can delay the transition to oral feeding and prolong hospitalization. Nonpharmacological interventions are increasingly used to support feeding readiness and neurobehavioral regulation. Exposure to breast milk odor has shown potential benefit. However, robust evidence from randomized controlled trials using validated outcome measures remains limited, particularly in the Indonesian context.

**Objective:**

This study aims to evaluate the effectiveness of breast milk odor on feeding cues and time to first successful breastfeeding in preterm infants admitted to the neonatal intensive care unit (NICU).

**Methods:**

This study is a single-blind randomized controlled trial currently underway with 2 parallel groups involving 96 preterm infants (gestational age 32‐34 weeks) admitted to the NICU. Participants are randomly assigned to receive either breast milk odor exposure or a neutral odor control intervention. The intervention is administered 3 times daily for 3 consecutive days before feeding sessions. Feeding cues (the primary outcome) are assessed using the validated Feeding Cues Follow-Up Form (FCF-UF) during each feeding session (9 assessments over the 3-day intervention period). Time to first successful breastfeeding is assessed daily from day 4 until successful breastfeeding is achieved, or for a maximum follow-up of 10 days. Statistical analysis will be conducted after data collection is completed, with significance set at *P*<.05.

**Results:**

This study was funded in May 2025. Recruitment commenced in December 2025 and was completed in March 2026. A total of 104 participants were enrolled. Data collection was completed in April 2026, and data cleaning and statistical analysis were completed in August 2026. The study findings are expected to be published in 2026.

**Conclusions:**

This trial will provide evidence on whether breast milk odor is an effective, low-cost intervention to improve feeding readiness and facilitate earlier breastfeeding initiation in preterm infants.

## Introduction

Prematurity remains a leading cause of neonatal morbidity and mortality worldwide. Globally, approximately 10.7% of all live births are preterm, and more than 6.7% of these infants die from complications related to prematurity [1]. Indonesia is among the countries with the highest preterm birth rates, contributing significantly to the burden in Southeast Asia [2]. In addition to respiratory complications and infections, delayed initiation of oral feeding is a major clinical challenge in preterm infants, often resulting in prolonged neonatal intensive care unit (NICU) stays, impaired growth, and increased psychosocial and economic burden for families [3].

Preterm infants frequently experience difficulties in initiating oral feeding due to immature oromotor reflexes and uncoordinated sucking, swallowing, and breathing patterns, leading to ineffective feeding and reduced tolerance [4]. These feeding difficulties are associated with physiological instability, including oxygen desaturation and bradycardia, and often prolong dependence on orogastric tube feeding, thereby delaying the transition to independent oral feeding and limiting early mother and infant interaction [5,6].

Developmental care approaches in the NICU emphasize optimization of the sensory environment to support neurodevelopment and feeding readiness. Among these, olfactory stimulation has gained increasing attention, as the olfactory system is one of the earliest sensory modalities to mature. Fetuses can detect and learn odors from amniotic fluid as early as the second trimester, facilitating early sensory learning [7]. Breast milk contains bioactive volatile compounds, including aldehydes, ketones, and fatty acid derivatives, which produce a distinctive and biologically relevant odor that varies between mothers and across lactation stages [8].

Recent evidence suggests that exposure to breast milk odor may enhance feeding readiness and behavioral responses in preterm infants. Studies [9] have reported significant improvements in feeding cues, earlier transition from tube to oral feeding, and improved abdominal perfusion following breast milk odor exposure. In addition, breast milk odor has been associated with reduced stress responses, improved physiological stability, decreased pain responses during procedures, and calming behavioral effects [10-12]. Improvements in respiratory outcomes, such as reduced apnea frequency, and enhanced weight gain have also been reported [13,14].

Although several previous studies have reported beneficial effects of breast milk odor on feeding behavior and physiological stability, many were limited by small sample sizes, single-center designs, nonrandomized methods, or inconsistent intervention procedures. In addition, the timing, frequency, and duration of olfactory stimulation varied substantially across studies, making direct comparison difficult.

Despite encouraging preliminary findings, the current body of evidence remains limited by substantial heterogeneity in study designs, including variations in intervention protocols (eg, timing, duration, and delivery methods of odor exposure); outcome measures; and sample characteristics. Although recent meta-analyses indicate a positive effect of olfactory and gustatory stimulation on feeding readiness, many included studies are constrained by small sample sizes, lack of adequate blinding, and potential bias, limiting the strength and generalizability of the conclusions [4]. Accordingly, additional randomized controlled trials using standardized methods are warranted.

While fully blinded randomized controlled trials are considered the gold standard to minimize bias, their implementation in NICU settings can be challenging due to the nature of sensory-based interventions. Therefore, this study adopts a single-blind randomized controlled design, ensuring methodological rigor while maintaining feasibility in clinical practice. The conceptual framework of this study is based on the premise that olfactory stimulation through breast milk odor can activate early sensory pathways, enhance feeding-related behavioral cues, and improve physiological stability, thereby facilitating the transition to oral feeding in preterm infants [7,9].

To our knowledge, no previous multicenter randomized controlled trial has evaluated breast milk odor using a standardized intervention protocol together with repeated feeding cue assessments using a validated instrument, Feeding Cues Follow-Up Form (FCF-UF), in the Indonesian NICU setting. This study is expected to provide context-specific evidence that may inform neonatal nursing practice in similar resource-limited settings.

This study aims to evaluate the effects of breast milk odor stimulation on feeding cues and time to first successful breastfeeding in preterm infants admitted to the NICU. We hypothesize that preterm infants receiving breast milk odor exposure will demonstrate significantly higher feeding cue scores and achieve successful breastfeeding earlier than infants receiving the neutral odor control intervention. The findings may provide evidence to guide neonatal nursing practice, particularly in resource-limited settings.

## Methods

### Design

This study is a multicenter, single-blind randomized controlled trial with 2 parallel groups. This study protocol was developed in accordance with the SPIRIT (Standard Protocol Items: Recommendations for Interventional Trials) 2025 Statement (Checklist 1), and the trial will be conducted and reported following the CONSORT (Consolidated Standards of Reporting Trials) 2025 Statement. This design allows prospective assessment of methodological rigor, scientific integrity, and ethical standards, as well as a retrospective validation of study implementation and reporting [15,16]. The overall study procedures are summarized in Figure 1.

**Figure 1. F1:**
[figure not shown]
Study flow diagram of the randomized controlled trial protocol. T0 indicates the baseline assessment; T1-T9 represent the 9 feeding cue assessment sessions conducted during the 3-day intervention period; T10 indicates the assessment of time to first successful breastfeeding.

### Setting

This study was conducted in the NICUs of 2 tertiary referral hospitals in Central Java, Indonesia: [name] Hospital in Yogyakarta and [name] General Hospital in Klaten. These NICUs were selected because they provide comparable standards of care for preterm infants, are equipped with comprehensive intensive monitoring facilities, and maintain a high rate of breastfeeding among preterm infants admitted to their units. Moreover, the selection was based on the high rate of preterm births in Central Java, ranging from 6% to 7% [17]. As tertiary referral hospitals, both NICUs manage a large volume of preterm infant admissions. Participants were recruited consecutively in both NICUs.

In both participating NICUs, preterm infants are initially fed via an orogastric or nasogastric tube according to standard neonatal care protocols. The transition to oral feeding is initiated when infants demonstrate physiological stability, coordinated suck-swallow-breath patterns, and feeding readiness as determined by the attending neonatologist and neonatal nurses. Once these criteria are met, breastfeeding attempts are routinely performed at each scheduled feeding session. During the study period, routine feeding management, including decisions regarding feeding advancement and breastfeeding initiation, will continue according to the standard clinical protocol in both the intervention and control groups. Breast milk odor exposure is provided as an adjunct to, rather than a replacement for, routine feeding care.

Eligible infants were identified daily through routine clinical screening and medical record review by trained NICU nurses and research assistants to standardize participant screening and recruitment.

### Participants

Preterm infants with a gestational age between 32 and 34 weeks were selected as participants in this study. As sucking, swallowing, and breathing reflexes begin to develop during this period but are not yet fully mature, targeted intervention is required to accelerate readiness for oral feeding while minimizing clinical variability and the risk of severe complications, such as severe hypoxia, intraventricular hemorrhage, and necrotizing enterocolitis (NEC) [18].

Other inclusion criteria were a minimum birth weight of 1,000 g; a stable hemodynamic condition, including infants receiving continuous positive airway pressure (CPAP); and infants receiving CPAP were eligible if respiratory support remained stable and olfactory stimulation could be administered safely without interrupting CPAP therapy; and infants who had not yet initiated oral feeding to ensure a uniform baseline of oral feeding development, which allowed the effects of the breast milk odor intervention to be measured without confounding from prior feeding experience [19]. In addition, written informed consent was obtained from the mothers prior to selection.

The exclusion criteria included infants with congenital abnormalities that could impair feeding ability, such as esophageal atresia or cleft lip and/or palate, metabolic disorders, a history of seizures, severe hypoxia, grade III or IV intraventricular hemorrhage, NEC, or prior exposure to other odors that could potentially interfere with the consistency of the breast milk odor intervention during the study period.

The screening process was conducted by a NICU nurse or research assistant through a review of the infant’s medical records and observation of the infant’s clinical condition. Once an infant met all established criteria, the parents were provided with a complete explanation of the study’s purpose and procedures, and informed consent was obtained before the infant was enrolled in the clinical trial. This criterion was intended to reduce baseline variability in feeding readiness. Recruitment followed a consecutive sampling approach, in which all eligible infants during the study period were approached to minimize selection bias.

### Sample Size Calculation

The sample size was calculated using G*Power version 3.1 based on an independent 2-group comparison (2-tailed independent-sample *t* test). Because previous studies investigating breast milk odor in preterm infants reported heterogeneous interventions, outcome measures, and effect estimates that were not directly comparable with the present study, a medium standardized effect size (Cohen *d*=0.50) was selected in accordance with Cohen’s recommendations for clinical research [20]. Assuming a 2-sided significance level of .05 and a statistical power of 80%, the minimum required sample size was 86 infants. To account for an anticipated 10% attrition rate, the final target sample size was increased to 96 infants, with 48 participants allocated to each group.

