## Results

This study was funded in May 2025. Recruitment commenced in December 2025 and was completed in March 2026, with a total of 104 participants enrolled. Baseline demographic and clinical characteristics, including gestational age, birth weight, and clinical stability, were collected for all participants. Data collection was completed in April 2026, followed by data cleaning and statistical analysis, which were completed in August 2026. No major deviations from the study protocol have been identified. The study findings are expected to be disseminated in 2026.

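### The sample size of 86 does not follow from its stated inputs: a 2-sided t test at d = 0.50, alpha .05 and 80% power needs 128, and the stated test has only 63% to 71% power

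*Protocol article*

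**What the plan says.** The Sample Size Calculation section of the protocol article gives every input of a two-sample calculation in G*Power 3.1:

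- Test: "based on an independent 2-group comparison (2-tailed independent-sample *t* test".
- Effect: "a medium standardized effect size (Cohen *d*=0.50) was selected", a conventional value chosen because earlier studies were judged not comparable.
- Error rates and result: "Assuming a 2-sided significance level of .05 and a statistical power of 80%, the minimum required sample size was 86 infants".
- Attrition: 10%, which raises the target to 96, 48 per group.

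The Abstract repeats the target ("2 parallel groups involving 96 preterm infants"). The Results section reports that recruitment closed "with a total of 104 participants enrolled". Randomization and Allocation gives a 1:1 ratio. Data Analysis plans a t test, or a Mann-Whitney test if normality fails, with a longitudinal analysis if repeated measurements are available.

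**The concern.** For a two-group t test, effect size, alpha, power and allocation ratio fix the sample size. All four are stated, and the figure printed beside them is well below what they imply. The 86 must be a total, because it becomes 96 with 48 in each group.

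This calculation is the only justification given for the size of the trial. If it is wrong, the trial claims 80% power for a medium effect that the stated test does not have. A non-significant result would then be read as fairly strong evidence against a medium effect when the risk of missing one is much higher than stated. The error does not bias the effect estimate or inflate the type I error. The harm lies in a misstated design property and in how a null result is interpreted.

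**Working it through.** **Inputs.** d = 0.50, 2-sided alpha = 0.05, power = 0.80, independent two-sample t test, 10% attrition (Sample Size Calculation); 1:1 allocation (Randomization and Allocation); 104 enrolled (Results).

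**Step 1: the attrition step.** 86 / (1 − 0.10) = 95.6, rounded up to 96. This reproduces, so the fault lies in the 86.

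**Step 2: approximate n per group.**

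n = 2 (z₀.₉₇₅ + z₀.₈₀)² / d² = 2 (1.960 + 0.8416)² / 0.25 = 62.8, so 63 per group and 126 in total.

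**Step 3: exact n per group.** Power comes from the noncentral t distribution with 2n − 2 degrees of freedom and noncentrality d√(n/2). The solution for 80% power is n = 63.77, so 64 per group and **128 in total**. At n = 64 the noncentrality is 0.5 × √32 = 2.828 and power is 0.8015; at n = 63 power is 0.795. The stated 86 is 128 − 86 = 42 infants short (42/128 = 33%). With the article's own attrition allowance, 128 / 0.9 = 142.2, so 143, or 144 for equal groups.

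**Step 4: can another reading give 86?**

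| Reading (d = 0.50, alpha .05) | Total N |
|---|---|
| 2-sided, 80% power (as stated) | 128 |
| 1-sided, 80% power | 102 |
| 2-sided, 70% power | 102 |
| 2-sided, 80% power, 2:1 allocation | about 144 |
| Paired or one-sample, 2-sided, 80% power | 34 |
| 2-sided, 90% power | 172 (86 per group) |

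None gives 86 in total. The last row may be where the number came from: 85.03 rounds up to 86 per group at 90% power. That is inference only, and it fits neither the stated 80% nor the use of 86 as a total.

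**Step 5: what the stated test delivers (2-sided .05).**

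| Analysed | Per group | Power at d = 0.50 | Chance of missing d = 0.50 | d detectable at 80% power |
|---|---|---|---|---|
| 86 | 43 | 63.0% | 37.0% | 0.611 |
| 94 (104 less about 10%) | 47 | 66.9% | 33.1% | 0.584 |
| 96 | 48 | 67.9% | 32.1% | 0.578 |
| 104 (no loss) | 52 | 71.4% | 28.6% | 0.555 |

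The rows assume equal groups. The article does not report how the 104 were split.

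**The case against.** The strongest counter-argument is that the primary outcome is measured nine times per infant and that Data Analysis allows a longitudinal analysis. If d = 0.50 refers to a single session and the mean of nine sessions is analysed, the variance falls by the factor (1 + 8ρ)/9, where ρ is the within-infant correlation. The article does not give ρ. Assuming the same correlation between every pair of sessions, power at 43 / 48 / 52 per group would be:

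| Assumed ρ | 43 | 48 | 52 |
|---|---|---|---|
| 0.5 | 87% | 90% | 92% |
| 0.6 | 81% | 86% | 88% |
| 0.7 | 76% | 81% | 84% |
| 0.8 | 71% | 76% | 80% |

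On that footing 86 infants suffice if ρ is about 0.62 or lower, and 104 suffice for ρ up to just under 0.8. This part stands: the 63% to 71% describes the t test named in the sample size section, not every analysis the trial might run. It does not rescue the 86, because that section uses no repeated-measures correlation and attributes the number to a plain t test.

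Two smaller points also stand. The 52/52 split is a natural assumption under 1:1 allocation but is not documented. The 96 was the real planning target and should not be erased. That recruitment is over limits the remedy, not the finding. Nor can the point be left to a separate analysis plan, because the figure and its inputs are printed together here.

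**Conclusion.** The concern holds. The stated inputs require 128 infants before attrition and 143 to 144 after it, not 86 and 96. For the stated test at d = 0.50, power runs from 63% (86 analysed) through 68% (the planned 96) to 71% (all 104 analysed in equal groups). The last figure is close to a best case for that test. Enrolling 104 does not reach the 128 needed before any loss. The result rests only on the article's own inputs and standard noncentral t theory; the 104 row also assumes a 52/52 split and no loss. This must be corrected, because the claim of 80% power is wrong as written and any reader with the same software can show it.

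**What to change.** Correct the statement in Sample Size Calculation. No further infants should be enrolled; recruitment has closed.

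1. Say that 86 was an error and that the stated inputs give 128 before attrition.
2. Keep 96 on record, there and in the Abstract, as the planned target, but no longer present it as giving 80% power at d = 0.50.
3. State why enrolment went to 104, and confirm the number per group.
4. Report what the achieved size supports. Possible wording, if the split is confirmed:

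> The planned target of 96 was based on a calculated minimum of 86 infants, which was an error; the stated inputs require 128. With 104 infants (52 per group), a 2-sided t test at the .05 level has 71% power for d = 0.50 and 80% power for d of about 0.555.

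5. If the primary analysis is the average over the nine sessions, base the power statement on that analysis, with the within-infant correlation stated and justified and with d defined on the matching scale.

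The cost is a few sentences. The stated power becomes less favourable; no data, procedure or analysis changes.

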### Randomization and Allocation

Randomization is performed using a 1:1 block randomization scheme with a fixed block size of 4 to ensure balanced group allocation. The allocation sequence was generated using a computer-generated randomization sequence by an independent statistician who was not involved in participant recruitment or outcome assessment.

Allocation concealment is maintained using sequentially numbered, sealed, opaque envelopes. Eligible participants are enrolled by a research assistant, who opens the next envelope in sequence only after enrollment to determine group assignment. This procedure ensures that allocation remains concealed until the point of assignment. Randomization was performed separately at each participating study site using the same allocation procedure to maintain balanced group assignment throughout the recruitment period.

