### Outcome Measures

The primary outcome of this study was feeding cues, as measured by the FCF-UF. Feeding cues were assessed 3 times daily during each feeding session over the 3-day intervention period (total of 9 assessments). The assessments were conducted using video recordings, which were evaluated by a blinded pediatric nursing specialist to ensure objectivity and reduce observer bias.

The secondary outcome was the time to first successful breastfeeding, defined as the duration (in minutes) from the onset of observable feeding cue behaviors until the infant achieved the first successful breastfeeding. Observable feeding cue behaviors included rooting, head turning toward the breast, mouth opening, and searching for the nipple following tactile stimulation. Successful breastfeeding is defined as effective latching onto the mother’s breast followed by coordinated sucking, swallowing, and breathing for a sustained period, as observed by trained clinical staff.

Although breastfeeding attempts may occur during routine clinical care during the 3-day intervention period, these routine attempts were not included in the assessment of the secondary outcome. To ensure a standardized observation period across all participants, the predefined secondary outcome (time to first successful breastfeeding) was prospectively measured beginning on day 4, after completion of the intervention. Observations were conducted daily for a maximum of 60 minutes per day and continued for up to 10 days or until successful breastfeeding was achieved.

This outcome was measured using a stopwatch starting from day 4 after completion of the intervention. The measurement of time to first successful breastfeeding therefore began after completion of the 3-day intervention period (day 4). Postnatal age and other relevant clinical variables were recorded and will be considered as potential confounders in the analysis.

All outcome data were recorded in structured electronic forms immediately after each assessment to ensure accuracy and completeness. The schedule of enrollment, intervention, and outcome assessments is presented in Table 1.

**Table 1. T1:** Schedule of enrollment, intervention, and outcome assessments.

Study phases	Day 0	Days 1‐3	Days 4‐10
Screening and eligibility	✓		
Informed consent	✓		
Randomization	✓		
Intervention (breast milk odor exposure)		✓^a^	
Feeding cue assessment (FCF-UF^b^)		✓^c^	
Time to first successful breastfeeding			✓^d^

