### Data Analysis

Data analysis will be conducted according to the intention-to-treat principle; therefore, all randomized participants will be included in the analysis according to their assigned groups, regardless of their adherence to the intervention. Outcomes will be analyzed using an independent *t* test for normally distributed data or the Mann-Whitney *U* test when normality assumptions are not met. If repeated measurements are available across multiple points, longitudinal analysis will be performed to more comprehensively assess response changes over time. For the secondary outcome of time to first successful breastfeeding, Kaplan-Meier survival analysis will be used, with between-group comparisons performed using the log-rank test. Infants who do not achieve successful breastfeeding within the 10-day observation period will be treated as censored observations. Intervention effects will be reported as the mean difference between groups, accompanied by effect sizes, using Cohen *d* to describe the magnitude of the intervention’s impact.

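### Allocation was stratified by site, but the named tests ignore site, and the promised covariate adjustment is neither specified nor carried into the Data Analysis section

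*Protocol article*

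**What the plan says.** Three sections of the Protocol article bear on this.

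- **Randomization and Allocation** describes 1:1 blocks of fixed size 4 and adds: "Randomization was performed separately at each participating study site using the same allocation procedure to maintain balanced group assignment throughout the recruitment period". There are two sites (Setting).
- **Outcome Measures** says: "Postnatal age and other relevant clinical variables were recorded and will be considered as potential confounders in the analysis". It names no model and does not list the other variables.
- **Data Analysis** names an independent t test, or Mann-Whitney U if normality fails. It adds a longitudinal analysis if repeated measurements are available, and Kaplan-Meier curves with "between-group comparisons performed using the log-rank test". Effects are to be reported as mean differences with Cohen d. No site term, stratum or covariate is stated.

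On what was recorded, Results says: "Baseline demographic and clinical characteristics, including gestational age, birth weight, and clinical stability, were collected for all participants". The Figure 1 legend says "T0 indicates the baseline assessment", without saying whether a feeding-cue score is part of it.

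**The concern.** Blocking within site balances the arms on site. If site also predicts outcome, the treatment estimate varies less than an unadjusted standard error suggests. The test then rejects too rarely under the null and loses power under the alternative. An analysis that follows the randomisation uses the gain that stratification was meant to give.

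Maturity raises a second, separate point. Gestational and postnatal age plausibly predict feeding readiness, but they were not stratified on. Leaving them out keeps type I error at its nominal level and costs only precision.

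Third, the statement on confounders has no counterpart among the named two-group tests, none of which carries a covariate. Because neither the variables nor the model are fixed, the covariate set could be chosen after the results are seen.

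**Working it through.** **The plan's own figure.** The calculation is "based on an independent 2-group comparison (2-tailed independent-sample *t* test", where "a medium standardized effect size (Cohen *d*=0.50) was selected". It concludes: "Assuming a 2-sided significance level of .05 and a statistical power of 80%, the minimum required sample size was 86 infants". It contains no site term and no covariates. Noncentral-t power for these inputs gives 63.8, so 64 per arm or 128 in total; the stated 86 does not reproduce. Only the attrition step does: 86/(1 − 0.10) = 95.6, rounded up to 96. At d = 0.50, power is 63% with 86 analysed, 68% with 96 and 71% with the 104 enrolled. That is a separate defect; it matters here because precision is already short.

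**A. Ignoring site.** Assumptions, none given in the documents: 48 per arm split evenly over two sites, a site difference of δ within-site SDs, and d = 0.50 in within-site SD units.

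- Total variance relative to within-site variance: v = 1 + δ²/4.
- The unadjusted standard error is too large by about √v, so type I error ≈ 2Φ(−1.96√v).
- Noncentrality: 0.50/√(2/48) = 2.449. Power is about Φ(2.449 − 1.96√v) unadjusted and Φ(2.449 − 1.96) = 69% with site in the model.

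Simulation of the same design (t test against a linear model with a site term) agrees:

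| δ (assumed) | v | Variance due to site | Type I, formula | Type I, simulated | Power, unadjusted vs with site (simulated) |
|---|---|---|---|---|---|
| 0.2 | 1.01 | 1% | 4.9% | 4.9% | 68.0% vs 68.3% |
| 0.5 | 1.0625 | 6% | 4.3% | 4.2% | 66.1% vs 68.2% |
| 0.8 | 1.16 | 14% | 3.5% | 3.5% | 63.0% vs 68.3% |
| 1.0 | 1.25 | 20% | 2.8% | 2.7% | 58.4% vs 67.6% |

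The power loss is about 0, 2, 5 and 9 points. Nothing was computed for the Mann-Whitney or log-rank test.

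**B. Leaving out prognostic covariates.** Here d = 0.50 is in total SD units, so the figures cannot be added to those in A. In A, 68% is the adjusted power; here it is the unadjusted power. Adjusted power uses the effect d/√(1 − R²) in the noncentral-t formula, with R² assumed:

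| Infants | R² = 0 | 0.10 | 0.20 | 0.30 | R² needed for 80% |
|---|---|---|---|---|---|
| 96 | 68% | 72% | 77% | 83% | about 0.25 |
| 104 | 71% | 76% | 81% | 86% | about 0.19 |

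**C. The sections side by side.** Allocation is by site, the named tests are not, and the promise on confounders has no analysis attached to it. The longitudinal analysis could carry site and covariates, but the article does not say that it will.

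**The case against.** **Adjustment is foreseen.** A reader might infer that the plan excludes all adjustment. The documents do not support that: Outcome Measures mentions confounders, and a longitudinal model for the nine assessments could include covariates. What stands is that adjustment is mentioned, left unspecified and not linked to the stated tests.

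**This is detail for an analysis plan.** A journal article may leave model terms and covariate lists to a document not shown, and the absence of a list alone would be no finding. But the article does fix the tests, and as stated they neither follow its randomisation nor deliver what it promises about confounders.

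**The site effect may be small.** Setting describes the two units as offering comparable standards of care, and gestational age is restricted to 32 to 34 weeks. This objection stands as to size: up to a 0.5 SD site difference the loss is about 0 to 2 points. It is no reason to leave the stratum out, since a site term costs one degree of freedom.

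**The unadjusted tests remain valid.** For covariates that were not stratified on, this is right: type I error stays nominal. It would be wrong to infer that omitting gestational or postnatal age makes the test conservative. Only ignoring site can do that, and only if site is prognostic.

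**Conclusion.** The point holds as a mismatch between three sections that should be reconciled, with a modest and uncertain cost.

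- **Site:** the loss runs from nothing to about 9 points of power over assumed site differences of 0.2 to 1.0 SD, with type I error falling from about 4.9% to 2.7%. These figures rest on an even site split and a site effect that the documents do not give.
- **Covariates:** the gain from adjustment at 96 infants is 4 to 15 points (68% to between 72% and 83%) for an assumed R² of 0.10 to 0.30.

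A reader might infer that the stated tests are conservative outright, or that adjustment would repair the power. Neither follows. Conservatism depends on site being prognostic. Adjustment reaches 80% power only with an R² of about 0.25 at 96 infants or 0.19 at 104, and it does not cure the error in the Sample Size Calculation, where the stated inputs call for 128 infants.

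**What to change.** Reconcile Randomization and Allocation, Outcome Measures and Data Analysis:

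1. Include site as a term in the primary model, including any longitudinal model, and as a stratum in the log-rank test.
2. Replace the open statement on confounders with a closed list of documented baseline covariates: gestational age, and postnatal age at randomisation. Add CPAP status or a T0 feeding-cue score only if confirmed as recorded at baseline. The article mentions CPAP only under eligibility and procedures, and does not say what T0 contains.
3. Report the unadjusted tests alongside.
4. State when the adjusted model was specified. Results says that statistical analysis was completed in August 2026, so a model introduced now cannot be presented as prespecified.
5. Add a Cox model only after the time scale is settled: Outcome Measures counts minutes from the onset of cues, while Data Analysis censors at the end of a 10-day observation period.

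The cost is one or a few degrees of freedom, some wording, and a short re-run of the analysis.
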